## Statistics

### Statistical methods

The primary goal of this study is to determine the rate of out-of-field N-site recurrences in nonirradiated lymph node levels after two years. The intervention is designed such that we expect a rate of out-of-field N-site recurrences in non-irradiated lymph node levels of < 10% (resulting in a value of 0.9 of the survival function at two years). The goal is to measure the cumulative probability of out-of-field recurrence with a precision resulting in a width of 10% of the 90% confidence interval of the Kaplan-Meier estimator at 2 years).

### Sample size calculation

120 patients will be included in this study. Under the assumption of no censoring or drop-outs, the intended width of 10% for the 90% confidence interval (from 0.84 to 0.94) for the survival probability of 0.9 can be obtained with 104 patients. By including 120 patients, we account for an amount of censoring or dropouts of 13%. The confidence interval was calculated for the log-minus-log transformation of the survival function using the asymptotic variance approximation as described in Nagashima et al. [45] and then back transformed.

### Statistical analyses

The primary endpoint will be evaluated according to the per-protocol treatment, although all primary analyses will follow both the per-protocol and intention-to-treat principles.

The primary endpoint “Out-of-field lymph node recurrence” will be reported as the Kaplan-Meier estimator for the time-to-event at 2 years. The calculation of the Kaplan-Meier estimator at 2 years will include the events detected at the 24-months follow-up visit (which may occur at 2 years +/- 1 month). Patients lost to follow-up and patients who die due to any cause are right-censored.

In addition to the overall rate of Out-of-field lymph node recurrences, we will analyze whether 1) Out-of-field lymph node recurrence was the initial cause for loco-regional failure, or whether 2) recurrence/persistence of the primary tumor or grossly involved lymph nodes present at baseline was observed simultaneously or prior to the Out-of-field lymph node recurrence. In case 1, irradiating the respective LNL electively may have prevented loco-regional failure. In case 2, loco-regional failure may have occurred irrespective of volume-de-escalation, and the Out-of-field lymph node recurrence may be due to lymphatic spread of the recurrent/persistent tumor. To determine the rate of “Out-of-field lymph node recurrences being the initial cause for loco-regional failure”, we will perform Kaplan-Meier analysis where patients with recurrence/persistence of the primary tumor or grossly involved lymph nodes present at baseline are right-censored.

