### Endpoints

The primary endpoint is the rate of out-of-field N-site recurrences 2 years after the end of the primary (chemo)radiotherapy treatment. An event towards the primary endpoint is defined as any N-site recurrence in non-irradiated LNLs.

Secondary endpoints include the rate of out-of-field N-site recurrences 3 years after the end of the primary (chemo)radiotherapy treatment (in direct analogy to the primary endpoint), loco-regional control, progression-free survival and overall survival. For patients with recurrence, we will analyze detailed patterns of failure in terms of time to event and location of the recurrence, distinguishing T-site recurrence, N-site recurrence or persistence of grossly involved lymph nodes, isolated N-site recurrences in electively treated LNLs, and isolated recurrences in unirradiated LNLs. In addition, we will analyze early (≤3 months after treatment) and late (>3 months after treatment) toxicities of treatment: assessed by grading of toxicities according to CTCAE v5 [40]. Assessment of toxicities will be performed weekly (1x/week) during radiotherapy and during every follow-up visit. Overall toxicity will be evaluated according to the TAME methodology [41]. Other secondary endpoints include blood examination, including full blood count with lymphocytes taken during routine examination before and after the last radiotherapy, and quality of life (QoL) assessed using the EORTC QLQ C30 and Head and Neck Module HN43 questionnaires at the start of treatment, as well as after completing treatment, and 6, 12 and 24 months after radiotherapy [42], [43]. The evaluation of dysphagia using the M.D. Anderson Dysphagia Inventory (MDADI) [44] at 12 and 24 months is a planned addition.

Tumour response on imaging is assessed according to the RECIST criteria. Persistence is defined as progressive disease (PD), stable disease (SD) or incomplete response of the primary tumour (local persistence/persistence of the primary tumour) or nodal metastases at baseline (nodal persistence). Recurrence is defined as new pathological lesions/disease (new lesions or new lesions after complete response before) of the primary tumour (local recurrence), previous pathological lymph nodes (known lymph nodes), new lymph nodes, or distant metastases.

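### Kaplan-Meier with competing events censored overstates the 2-year cumulative probability: slightly, and arguably by intent, for the primary endpoint; more clearly for the initial-cause rate, where it estimates neither incidence nor a valid net risk

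*Protocol article*

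**What the plan says.** All references are to the protocol article.

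- **Target.** Under Statistical methods: "The goal is to measure the cumulative probability of out-of-field recurrence". The same sentence sets the precision in terms of the Kaplan-Meier estimator at 2 years. The expected rate is below 10%, expressed as "resulting in a value of 0.9 of the survival function at two years".
- **Event.** Under Endpoints: "An event towards the primary endpoint is defined as any N-site recurrence in non-irradiated LNLs".
- **Primary estimator.** Under Statistical analyses, the endpoint "will be reported as the Kaplan-Meier estimator for the time-to-event at 2 years". On censoring: "Patients lost to follow-up and patients who die due to any cause are right-censored". Death is thus handled in the same way as loss to follow-up.
- **Initial-cause analysis.** In the same section: "we will perform Kaplan-Meier analysis where patients with recurrence/persistence of the primary tumor or grossly involved lymph nodes present at baseline are right-censored". Just before this, the plan says that an out-of-field recurrence seen with or after such a failure may have spread from the recurrent or persistent tumor.

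No competing-risk estimator is named, and no target of the form 'risk if nobody died or failed elsewhere' is declared.

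**The concern.** A patient lost to follow-up can still recur; a patient who has died cannot. A patient whose primary tumor or baseline nodes have already failed can no longer have an out-of-field recurrence as the initial cause of failure. Both are competing events. Censoring them makes one minus Kaplan-Meier estimate the risk in a population where those events do not occur, and only if they are independent of the event of interest. It does not estimate the proportion of treated patients who have the event by 2 years.

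The primary result will be read against the expectation of less than 10%. The initial-cause rate is the plan's evidence on how many loco-regional failures elective irradiation might have prevented. If what is being estimated is unclear, that reading is unclear too.

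**Working it through.** **1. The plan's own figure.** S = 0.9, 90% interval, log-minus-log scale, no censoring (Sample size calculation).

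se = sqrt((1−S)/(nS)) / |ln S|. With n = 104: sqrt(0.1/93.6)/0.10536 = 0.310. The limits are exp(−exp(ln(0.10536) ± 1.645 × 0.310)) = 0.839 and 0.939, a width of 0.0997. With n = 103 the width is 0.1002, so 104 is the smallest n. Then 104/0.87 = 119.5, rounded up to 120. The plan's figures reproduce.

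**2. Kaplan-Meier against cumulative incidence.** Assume constant, independent hazards. Let p_k be the 2-year risk of event k acting alone, l_k = −ln(1−p_k), and L the sum of the l_k. One minus Kaplan-Meier targets p_1. The cumulative incidence is

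CIF = (l_1/L) × (1 − exp(−L)).

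The article gives no expected death or failure rate for this trial, so every competing rate below is an assumption.

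*Primary endpoint, Kaplan-Meier estimate 10.0% (l_1 = 0.1054), death competing:*

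| Deaths by 2 years | CIF | Gap (points) |
|---|---|---|
| 10% | 9.5% | 0.5 |
| 13% (whole allowance) | 9.35% | 0.65 |
| 15% | 9.2% | 0.8 |
| 20% | 9.0% | 1.0 |

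The 13% row: l_2 = 0.1393, L = 0.2446, CIF = 0.4307 × (1 − 0.783) = 0.0935.

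In the other direction, take a true incidence of 10% with 5%, 10%, 15%, 20% or 30% of patients having the competing event first. One minus Kaplan-Meier is then 10.3%, 10.6%, 10.9%, 11.2% or 12.0%.

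*Initial-cause rate, Kaplan-Meier estimate 10.0%, death and other loco-regional failure competing:*

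| Deaths | Other failure | CIF | Relative excess |
|---|---|---|---|
| 13% | 7.4% | 9.0% | 11% |
| 15% | 10% | 8.8% | 14% |
| 15% | 20% | 8.3% | 20% |
| 20% | 25% | 7.9% | 27% |

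The first row: l_3 = −ln(0.926) = 0.0769, L = 0.1054 + 0.1393 + 0.0769 = 0.3215, CIF = 0.3277 × (1 − 0.7251) = 0.0901. The 7.4% is the loco-regional recurrence in the reduced-volume patients of a postoperative trial cited in the Discussion. It is an imperfect proxy.

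The initial-cause events are a subset of the out-of-field events, so 10% is a high starting point. At 3.5%, near the 2.8% and 3.6% cited in the Discussion, the first row's assumptions give 3.15%, a gap of 0.35 points.

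**3. If net risk were intended.** One minus Kaplan-Meier is a valid net risk only under independent censoring. A simulation with a shared gamma frailty (baseline hazards 0.055 per year for out-of-field recurrence and 0.10 for other failure) gave:

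| Frailty variance | CIF | 1 − Kaplan-Meier | True net risk |
|---|---|---|---|
| 0 | 9.5% | 10.5% | 10.5% |
| 1 | 8.4% | 9.1% | 9.9% |
| 2 | 7.6% | 8.2% | 9.5% |

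With positive dependence, Kaplan-Meier lies above the incidence and below the net risk. The frailty is one illustrative form of dependence; the plan does not specify one.

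**The case against.** The strongest reply concerns the 10% figure. According to the Introduction and the section on previous work, it is a modelled risk that occult metastases are present in the non-irradiated levels. Later death does not reduce that risk, whereas a cumulative incidence falls as more patients die and so would flatter de-escalation against it. The goal sentence also names the Kaplan-Meier estimator. For the primary endpoint a net risk is therefore an arguable target. This stands, and it is why Kaplan-Meier should be kept there.

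It is also fair that no decision turns on the choice. The objective is precision, there is no test or success criterion at 10%, and the enrolment stop is based on an event count. The primary shift makes the new approach look worse, and it is small beside an interval half-width of about 5 points. This stands too.

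A reader might infer relative overstatements of 14% to 27% for the initial-cause rate. Those need 10% to 25% other failure. The figures the article cites are lower: 4.2% local and 2.9% regional failure at 5 years after standard treatment, and 7.4% loco-regional recurrence with reduced volume. These are imperfect proxies, but they do not support the larger values as the headline.

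The net-risk argument does not carry over to the initial-cause analysis, because the plan's own account of how such recurrences arise undermines independent censoring.

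**Conclusion.** The point holds, with different force for the two analyses.

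**Primary endpoint.** One minus Kaplan-Meier overstates the actual cumulative probability. A Kaplan-Meier estimate of 10.0% corresponds to about 9.35% if the full 13% allowance were deaths, and to 9.5% to 9.0% for 10% to 20% deaths. A reader might infer that the primary estimate is simply wrong. The documents do not support that: a net risk is a defensible comparator for the modelled 10%. What is missing is a statement of which risk is meant, and the incidence beside it.

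**Initial-cause rate.** Neither reading rescues the estimator. As an incidence it is too high: 10% corresponds to about 9.0% with 13% deaths and 7.4% other failure, and the gap grows with higher assumed failure rates. As a net risk it is too low under positive dependence. An unqualified statement of upward bias would therefore also be inexact, since the direction depends on the target.

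The sizes rest on constant, independent hazards and assumed competing rates. For the incidence target the direction does not depend on those assumptions, since one minus Kaplan-Meier cannot lie below the cumulative incidence.

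**What to change.** 1. **Initial-cause rate:** replace Kaplan-Meier with the Aalen-Johansen cumulative incidence at 2 years. Death and prior or simultaneous other loco-regional failure are competing events.
2. **Primary endpoint:** report the Aalen-Johansen cumulative incidence with death as a competing event and a 90% log-minus-log interval. Report the planned Kaplan-Meier estimate beside it, labelled as the net-risk estimate to compare with the model's 10%.
3. **Censoring in the cumulative-incidence analyses:** only loss to follow-up and end of data.

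The cost is a few sentences of analysis text and standard software, with no new data. With complete follow-up the cumulative incidence has the same binomial variance, so 104 inflated to 120 stands. Recruitment is estimated to finish in January 2027, so the change can be specified before the 2-year analysis.

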### Safety interim analysis

If at any point in time during recruitment, the total number of events reported to the sponsor exceeds 20, no additional patients will be enrolled.

We will perform a safety interim analysis when 60 patients have been enrolled.

## Discussion

Our clinical trial aims to personalize the radiotherapy treatment of patients with oropharyngeal carcinoma. Our goal is to reduce treatment volume and herewith reduce radiotherapy-associated short-term and long-term side effects to improve patients’ quality of life. In our trial we test the hypothesis that the elective irradiation treatment volume can be personalized and reduced in most patients based on T-category and midline extension of the primary tumor and clinical involvement of the lymph nodes.

Previous de-escalation trials in squamous cell head and neck cancers, such as DIREKHT, EVADER, REWRITE and Van den Bosch et al., have shown promising locoregional control and overall survival rates, with improvement of toxicity [21], [22], [23], [46], [47]. DIREKHT included postoperative oral cavity, oropharynx, hypopharynx or larynx patients, and de-escalated treated volume, radiation dose, or both. Volume de-escalation consisted of omission of the contralateral elective nodal irradiation in case of contralateral pN0 or contralateral cN0 for lateralized tumors. Of the patients treated with reduced volume, 7.4% developed a locoregional recurrence. Four out of 143 patients (2.8%) that were treated with omission of the elective contralateral neck irradiation developed a regional recurrence in a contralateral neck node [21]. REWRITE de-escalated treatment for mainly laryngeal and oropharyngeal SCC patients by only including the LNLs directly adjacent to the primary tumor or involved LNLs. Two patients (3.6%) had a disease progression in the non-irradiated neck after after one year [22]. The phase III trial from Van den Bosch et al. included patients with oropharyngeal, hypopharyngeal and laryngeal SCC, and de-escalated treatment by reducing the dose to the elective neck to 35 Gy. The 2-year recurrence rate in electively irradiated nodes in the dose reduction groups was 4.9% compared to 4.3% in the control group [47], [48]. The phase II EVADER-trial resembles the DeEscO trial the most regarding de-escalation strategies but included only HPV-related oropharyngeal SCC patients. Here, volume-reduced ENI was tailored to primary location, T-category, and distribution of involves nodes. In total, five local recurrence events were observed, including one out-f-field regional control event [23].

HPV-related oropharyngeal SCC is associated with a better prognosis than patients with HPV-negative tumors [49]. Previous de-escalation efforts have distinguished de-escalation strategies between HPV-positive and HPV-negative patients [50]. Our trial instead includes patients irrespective of HPV-status with identical definitions of the CTV-N. The rationale is two-fold. First, the primary endpoint is N-site recurrences in unirradiated LNLs rather than locoregional control or overall survival. Second, based on our data on LNL involvement and the statistical model, we do not expect a substantial difference in the risk for occult metastases between HPV-positive and HPV-negative disease. Although HPV-positive tumors show a higher prevalence of lymph node involvement, especially for early T-category tumors, the probability of occult metastases conditioned on the clinical nodal status of an individual patient is similar according to our analysis.

A limitation of our trial is the lack of a control group. In part, the single-arm design is justified by the choice of the primary endpoint. Out-of-field N-site recurrence is an event specific to volume-de-escalation, which is expected to be very rare in a control group treated according to current ENI guidelines. Hence, the value of a control arm regarding the analysis of the primary endpoint is very limited. However, a randomized trial with a control group would have strengthened the analysis of secondary endpoints. Demonstrating toxicity reductions or non-inferiority in local control or overall survival may require a randomized trial. Because of the limited number of patients newly diagnosed with oropharyngeal cancer in Switzerland, this was considered outside the scope of this investigation.

In addition, the trial has limitations due to its pragmatic approach. Diagnostic procedures and follow-up are mostly limited to what is part of routine clinical care and we do not perform rigorous clinical trial QA during the trial. In addition, the trial protocol allows for small variations in institutional practice between the participating centers. For example, the use of an intermediate dose level in the PTV-2 is at the local investigator's discretion. However, given the well-defined dose prescriptions for PTV-1 and PTV-3, the dose fall-off around PTV- will likely be similar for patients planned with the intermediate dose and those treated without it. Hence, the addition of the intermediate dose is not expected to significantly impact dose distributions, toxicity, or quality of life.

Our research group is currently working on further improving the statistical models and extending the model to other tumor entities in the head and neck area, such as the oral cavity, hypopharynx, and larynx. Potentially, the personalization of the elective lymphatic irradiation volume could in the future also be extended to other tumor types with lymphatic spread patterns.

## Planned timeline

The first center opened in January 2025. Three other centers opened in February 2025. One other center opened in July 2025. The last center is planned to follow shortly afterwards. Recruitment is estimated to be completed by January 2027.

## Ethics committee approval

Ethical approval was obtained on 21/01/2025, BASEC-Nr 2024-01936. The study will be performed in accordance with the Declaration of Helsinki, the principles of Good Clinical Practice, the Human Research Act and the Human Research Ordinance, as well as other relevant local regulations.

## Consent for publication

Written informed consent is obtained from each participant prior to their inclusion in the study.

## Availability of data and materials

The previously collected multi-institutional dataset of 598 oropharyngeal SCC patients in whom the detailed patterns of lymph node involvement are reported is publicly available on https://www.LyProX.org. The data collected during the clinical trial will be published and be publicly available, after evaluation of each endpoint and concurrently with respective publications.

## Ethics approval and consent to participate

Ethical approval was obtained on 21/01/2025, BASEC-Nr 2024-01936. The study will be performed in accordance with the Declaration of Helsinki, the principles of Good Clinical Practice, the Human Research Act (HRA) and the Human Research Ordinance (HRO), as well as other relevant local regulations. Written informed consent is obtained from each participant prior to their inclusion in the study.

